#### Interviews

Twenty participants from the intervention group will be interviewed postintervention and 12 months postrandomization, and 20 participants from the usual care group will be interviewed 12 months postrandomization. Participants will be asked to participate sequentially until the recruitment target is reached. Interviews will be conducted over the telephone or face to face, depending on the participant's preference. The postintervention interview will focus on gaining perceptions of (1) how the intervention was delivered; (2) aspects of the intervention individuals found useful; and (3) compliance with the intervention, how aspects of the intervention were used, and recommendations for change. The 12-month interview will explore (1) experiences of the randomization process, (2) general perceptions of the trial, and (3) the personal return-to-work process of each individual. Members of both groups will be asked about their experiences and how this may have impacted their return to work as well as any additional support received regarding return to work.

#### Data Management

To maintain confidentiality, all participants will be given a unique identifier that will be used on all hard copy and database records. Patient names will not be used. Clinical and research government guidelines will be followed for safe and confidential storage of participant personal data (such as password-protected data files), to which only the research team directly involved in the study will have access. If a participant withdraws from the study, identifiable data which has already been collected with consent would be retained and used in the study, but no further data would be collected from the participant.

### Analysis Plan

#### Qualitative Analysis

Although this is a mixed-methods study, the main focus of the analysis of the study will be qualitative. Interviews will be recorded, transcribed verbatim, and analyzed using the framework method [46] to identify emergent themes.

#### Quantitative Analysis

The purpose of this feasibility study is not hypothesis testing. Furthermore, it is anticipated that the sample size will be underpowered to undertake the full analysis that would be used in a full trial (analysis of covariance adjusting for baseline values). Baseline characteristics will be reported as mean and standard deviations or medians and interquartile ranges for continuous data and as n (%) for categorical data. Differences between the intervention and control groups for the primary outcome measure will be examined. Secondary outcome measures will be assessed using independent samples *t* tests (significance level set at .05).

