**Objective:**

The primary objective is to assess the feasibility and acceptability of a theoretically led workbook intervention designed to support cancer patients in returning to work to inform a fully powered randomized controlled trial (RCT).

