**Methods:**

This is a multicenter feasibility RCT where the main analysis uses a qualitative approach. Sixty participants (aged 18-65 years) who have received a diagnosis of cancer and who intend to return to work will be randomized to either the WorkPlan intervention group or a usual care group (ratio 1:1). Participants in the intervention group will receive a guided workbook intervention (which contains activities aimed at eliciting thoughts and beliefs, identifying targets and actions, and concrete steps to achieve goals) and will receive telephone support over a 4-week period. The primary outcome measure is time taken to return to work (in days), and secondary outcome measures include mood, quality of life, illness perceptions, and job satisfaction. Data will be collected through postal questionnaires administered immediately postintervention and at 6- and 12-month follow-ups. In addition, interviews will be undertaken immediately postintervention (to explore acceptability of the intervention and materials) and at 12-month follow-up (to explore perceptions of participation in the trial and experiences of returning to work).

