## Methods

### Eligibility Criteria

Inclusion criteria: patients who have received a diagnosis of breast, gynecological, urological, or bowel cancer that has not been classified as metastatic disease or recurrence; are at least 2 weeks posttreatment initiation; are aged 18 to 65 years; were working at the time of diagnosis; and are not currently working but intend to return to work.

Participants will be recruited to the study from multiple UK hospital sites. We aim to recruit 60 participants who will be randomized into either the intervention or the usual care group. There are currently no clear guidelines for estimating an appropriate sample size for feasibility studies. This is not a hypothesis testing study; the sample size is based on pragmatic assumptions around feasible recruitment figures and the number of participants required to estimate the key parameters around the feasibility of a full RCT.

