## Discussion

### Principle Considerations

There is currently no available standardized return-to-work intervention focused on targeting cancer patient beliefs. Previous research [47,48] has demonstrated that both cancer patients and organizations report that such an intervention would be invaluable to facilitate return to work and ensure work retention. Undertaking a feasibility study is critical to inform the planning of a larger, fully powered RCT to improve work-related outcomes among cancer survivors. The results of the study will be used to modify the trial materials and methodology if required and determine likely recruitment and retention rates for a larger trial. If appropriate, the results of the feasibility study will be used to estimate a sample size calculation for a future (appropriately powered) RCT of the intervention with a longer follow-up period. If a fully powered RCT were to demonstrate that the WorkPlan intervention is more effective in supporting return to work than usual care, this would allow us to implement a valuable, cost-efficient tool to support people who have received a diagnosis of cancer in planning and achieving supported return to work as well as greater satisfaction with work and the return-to-work process.

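### The study disclaims hypothesis testing, yet its quantitative plan fixes t tests at a .05 significance level for the secondary outcomes

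*Protocol article*

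**What the plan says.** Two places in the protocol article say that the study does not test hypotheses. Under Eligibility Criteria, where 60 participants are justified: "This is not a hypothesis testing study; the sample size is based on pragmatic assumptions around feasible recruitment figures". At the start of Quantitative Analysis: "The purpose of this feasibility study is not hypothesis testing". The next sentence of Quantitative Analysis expects the sample to be underpowered for the baseline-adjusted analysis of covariance that a full trial would use.

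The same paragraph then gives the secondary outcomes independent samples t tests, with "significance level set at .05". It does not say how many outcomes or time points are tested. For the primary outcome it says only that group differences will be looked at, and names no test and no significance level.

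On objective and outcome, the abstract states: "The primary objective is to assess the feasibility and acceptability of a theoretically led workbook intervention". The abstract's Methods nevertheless label time to return to work, in days, as the primary outcome measure without qualification. The Study Outcomes section presents the same variable as one of the main outcomes of a full trial, being used here.

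**The concern.** The only function of a significance level is to divide results into significant and non-significant, which is what the two disclaimers say the study will not do. An analyst cannot follow both instructions, so one of them has to change.

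The interpretation of the secondary outcomes is at stake. In a sample this small, a moderate real effect would often come out as non-significant and might be read as a reason not to proceed. Among several uncorrected tests, a chance positive might be read as early evidence of benefit. An estimate with its interval shows the uncertainty directly.

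**Working it through.** The article derives no power or precision figure and calls its sample size pragmatic, so there is no stated figure to reproduce. The calculations below show what the t tests would deliver.

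**Inputs from the article**
- 60 participants, allocated 1:1, so 30 per arm (Eligibility Criteria; Allocation and Stratification).
- Independent samples t test at .05 (Quantitative Analysis), taken here as two-sided because sidedness is not stated.
- Three post-baseline time points: 4 weeks, 6 months and 12 months (Study Outcomes).
- Secondary outcomes: three named in Study Outcomes, four domains named in the abstract, and eight instruments administered.

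**Assumptions, not in the article**
- True effects of 0.3, 0.5 and 0.8 SD.
- No loss (30 per arm) or 20% loss (24 per arm).
- Independent tests, for the false-positive calculation.

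**Power.** With n per arm, the test statistic follows a noncentral t distribution with 2n − 2 degrees of freedom and noncentrality d × √(n/2). For n = 30, √15 = 3.873, so the noncentrality is 1.162, 1.936 and 3.098 for the three effects.

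| Assumed effect | 30 per arm | 24 per arm |
|---|---|---|
| 0.3 SD | 21% | 17% |
| 0.5 SD | 48% | 40% |
| 0.8 SD | 86% | 77% |

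The normal approximation gives 21%, 49% and 87% at 30 per arm, which agrees. The effect detectable with 80% power is (1.960 + 0.842) × √(2/n): 0.72 SD for n = 30 and 0.81 SD for n = 24. An effect of 0.5 SD would need 63 per arm for 80% power, about twice the planned number. Two of the eight instruments are completed only by participants who have returned to work, so their power would be lower than shown.

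**False positives.** With k independent tests at .05 and no true effect, the chance of at least one significant result is 1 − 0.95^k, and the expected number is 0.05k.

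| Reading of the plan | k | Chance of at least one | Expected number |
|---|---|---|---|
| Three outcomes in Study Outcomes, one time point | 3 | 14% | 0.15 |
| Four domains in the abstract, three time points | 12 | 46% | 0.6 |
| Eight instruments, three time points | 24 | 71% | 1.2 |

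The expected number does not depend on independence. The chance of at least one does, and it is lower when the scales are positively correlated, as mood, illness perception and quality-of-life scales are likely to be.

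**Precision if intervals are reported instead.** With 30 per arm, the 95% half-width for a difference in means is 2.00 × √(2/30) = 2.00 × 0.258 = 0.52 SD. An interval of that width shows at once that the study cannot settle whether a moderate effect exists.

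**The case against.** The strongest defence is that the .05 level is a reporting convention in a study that openly calls itself underpowered. No progression decision is tied to a p-value. Principle Considerations gives the results other uses: to modify materials and methods, to "determine likely recruitment and retention rates for a larger trial" and, if appropriate, to inform a sample size. On this view, faulting the absence of multiplicity control in a non-confirmatory study adds little. That last part stands: a correction is not the remedy, and the harm lies in how results may be read, not in a built-in decision rule. The defence does not remove the contradiction. An unseen analysis plan would not remove it either, because both statements are in the published text.

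Three stronger readings are tempting and not supported.

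- **The primary outcome is also tested at .05.** A reader might infer this from its place in the same paragraph. The text attaches the t tests and the level to the secondary outcomes only.
- **Recruitment, retention and completeness are not estimated.** A reader might infer this because Quantitative Analysis does not list them. Aims 1, 2 and 4 under Current Study commit to checking completion of the materials, observing recruitment against monthly targets and determining retention by arm to 12 months, and Principle Considerations repeats recruitment and retention. How they are tabulated, and with what interval, is detail that an article may leave to the full protocol or analysis plan.
- **At least 24 tests will be run.** The article does not equate its secondary outcomes with all eight instruments, nor say that every time point is tested. The 71% is an upper-end scenario, not a floor.

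**Conclusion.** The point holds as a contradiction in the stated analysis rule. The article says "This is not a hypothesis testing study" and then prescribes significance tests at a fixed level for the secondary outcomes.

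The practical size depends on assumptions that the article does not supply. Power at 30 per arm runs from about 21% to 86% across effects of 0.3 to 0.8 SD. The chance of at least one false positive runs from about 14% to 71% across 3 to 24 independent tests. No sample-size or power figure in the article is wrong, because none is derived.

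The label on the primary outcome is a lesser matter of consistency. The abstract presents a clinical outcome as primary in a study whose primary objective is feasibility and acceptability, but Study Outcomes already makes clear that it is carried over from a future full trial.

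**What to change.** - In Quantitative Analysis, delete the .05 significance level and the t tests. State that between-arm differences in secondary outcomes will be reported as estimates with 95% confidence intervals, without p-values, and are exploratory.
- In the abstract's Methods, label days to return to work as the candidate primary outcome of the full trial, in line with Study Outcomes.

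Both are wording changes. They need no extra data, participants or follow-up, and the planned analysis does not start until April 2017. The price is that no p-values can be quoted for the secondary outcomes.

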### Allocation and Stratification

The researchers will randomize participants into one of the two arms using a central online and text system, Sealed Envelope (Sealed Envelope Ltd), at a ratio of 1:1 between the intervention group and usual care group. During the randomization process, participants will be stratified by age (18-50 or 51-65 years) and cancer type (breast, bowel, gynecological, or urological). Patients with different cancer diagnoses may have specific impairments or side effects due to the location of the cancer or the treatments received. Hence, stratifying for cancer type balances out any effects that might be due to this variable. Treatments undertaken during the follow-up period will be monitored in both arms of the trial. Participants are informed about their group allocation (guided intervention or usual care), and participants allocated to the usual care group will be informed that they will be offered the workbook after the 12-month follow-up.

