### Data Collection

#### Study Outcomes

The main outcome measures of a full RCT will be used (eg, number of days to return to work and satisfaction with the return-to-work process). At each time point, participants will be asked to recall the date of return to work (paid or unpaid employment, different job, reduced hours/salary, full-time or part-time). Any changes in working status and duties will be documented as will specific reasons for nonreturn to work (eg, unavailability of job, ongoing medical concerns) to determine whether to incorporate specific reasons for nonreturn as measures in a full trial. Secondary outcome measures include mood, satisfaction with return to work, and satisfaction with the return-to-work process. Although not appropriate for a feasibility trial, we would aim to undertake subgroup analysis of the primary outcome measure by cancer type/site in a future definitive RCT.

Data will be collected at 4 time points during the study: baseline, 4 weeks (postintervention), and 6- and 12-month follow-ups. At each time point participants will complete the following questionnaires:

Illness Perceptions Questionnaire-Revised [37]Brief Illness Perception at Work Scale [38]Hospital Anxiety and Depression Scale [39]Work Ability Index [40]Satisfaction with return to work if returned to work (single item)Satisfaction with Work Scale [41] (if returned to work)EQ-5D-5L (Quality of Life) [42]Visual Analogue Scale measure of Quality of Life (single item) [43]

Questionnaire packs will be mailed to participants with a prepaid self-addressed envelope. In addition, participants will be asked to provide details of their use of services and information via text message. A maximum of 4 text messages will be sent to participants at the end of each month for the duration of the study to gather information on their current work status and healthcare utilization. Monthly intervals were chosen because research shows that memory of general practitioner appointments is around 4 weeks, so we could not rely on accurate recall of healthcare utilization at 6-month follow-ups [44,45]. The text-based service can also be used for reminders to participants to complete and return questionnaire packs if there is missing data.

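### Low power is given as the only reason for leaving ANCOVA to the full trial, yet for secondary scores with a baseline value the unadjusted t test is usually the less precise choice

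*Protocol article*

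**What the plan says.** The Quantitative Analysis section states that the study is not for hypothesis testing. It adds that "it is anticipated that the sample size will be underpowered to undertake the full analysis that would be used in a full trial", and identifies that analysis as "analysis of covariance adjusting for baseline values". Two sentences later it says "Secondary outcome measures will be assessed using independent samples" t tests at the .05 level. No covariate is named for these comparisons.

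The other relevant facts are elsewhere in the article:

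- Study Outcomes: "Data will be collected at 4 time points during the study: baseline, 4 weeks (postintervention), and 6- and 12-month follow-ups". The illness perception scales, HADS, Work Ability Index, EQ-5D-5L and quality-of-life visual analogue scale are listed for every time point. The two work-satisfaction measures in that list are asked only of people who have returned to work.
- Eligibility Criteria: "We aim to recruit 60 participants who will be randomized into either the intervention or the usual care group". Participants are not working at entry.
- Allocation and Stratification: allocation is "at a ratio of 1:1 between the intervention group and usual care group", stratified by age group (two levels) and cancer type (four levels), on the ground that "stratifying for cancer type balances out any effects that might be due to this variable".

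**The concern.** Read in sequence, the section sets ANCOVA aside because the sample is small and falls back on the t test. That reasoning is reversed. Both methods estimate the same difference between arms from the same participants. Adjusting for a baseline score that predicts the outcome removes part of the residual variance, so a sample too small for ANCOVA is generally smaller still, in effect, for a t test.

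What is at stake is modest but real. Intervals for mood, quality of life and similar scores would be wider than they need be. Chance baseline differences, which are to be expected with about 30 per arm, would stay in the estimates. The study would also miss the chance to rehearse the analysis it names for the definitive trial, and a mistaken rationale could carry over into planning that trial.

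**Working it through.** **No figure to reproduce.** The sample size is pragmatic. The article gives no power, effect size, SD or baseline-to-follow-up correlation.

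**Inputs from the article.** N = 60, 1:1, so n = 30 per arm; significance level .05.

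**Assumptions.** Two-sided test; standardised effect d = 0.5; baseline-to-follow-up correlation r from 0 to 0.7; 20 to 30 completers per arm.

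**t test.** The noncentrality is d × √(n/2) = 0.5 × √15 = 1.936, on N − 2 = 58 df. Power is 47.8%.

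**ANCOVA on one baseline score.** The variance of the difference is multiplied by V = (1 − r²) × [1 + 1/(N − 4)]. The second term, 57/56 = 1.018, allows for chance imbalance in the covariate. Noncentrality is 1.936/√V on N − 3 = 57 df.

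| r | V | √V (SE relative to t test) | ANCOVA power | Difference detectable at 80% power |
|---|---|---|---|---|
| 0 | 1.018 | 1.009 | 47.1% | 0.74 SD |
| 0.3 | 0.926 | 0.962 | 50.7% | 0.71 SD |
| 0.5 | 0.763 | 0.874 | 58.7% | 0.64 SD |
| 0.7 | 0.519 | 0.720 | 75.2% | 0.53 SD |

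The t test's detectable difference is 0.74 SD. The worst case for ANCOVA (r = 0) costs 47.8 − 47.1 = 0.7 percentage points of power and a standard error about 1% larger. At r = 0.5 the standard error is about 13% smaller and power rises by 10.9 points. At r = 0.7 the figures are 28% and 27.4 points.

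**Simulation check (20,000 trials per setting).** t test against ANCOVA: 47.4% and 46.8% (r = 0), 47.8% and 51.2% (r = 0.3), 47.9% and 59.2% (r = 0.5), 48.2% and 75.1% (r = 0.7). These agree with the formula.

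**Break-even.** The two methods have equal power at r = 0.135 with 30 per arm, and at r = 0.168 with 20 completers per arm.

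**Fewer completers.** With 20 per arm and d = 0.5, t-test power is 33.8%, against 33.0% (r = 0), 41.9% (r = 0.5) and 56.6% (r = 0.7) for ANCOVA. The ordering is unchanged.

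**Adding the stratification factors.** Age group uses 1 df and cancer type 3, so with the baseline score there are 5 covariate df. The imbalance term becomes 1 + 5/52 = 1.096, on 53 df. With R the joint correlation of all covariates with outcome, power is 44.3% (R = 0), 47.8% (R = 0.3), 55.5% (R = 0.5) and 72.0% (R = 0.7). Break-even is R of about 0.30, or about 0.38 with 20 completers per arm.

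**The case against.** Several points on the other side have force.

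- **The causal link is inferred.** The article never says outright that t tests replace ANCOVA for lack of power. The sentence can be read as saying only that 60 participants are too few for a confirmatory analysis. That is possible, but it names ANCOVA specifically, the t tests follow, and no other reason is offered. Even on the kinder reading the wording misleads.
- **The t test is valid.** A reader might infer bias or an inflated error rate. Neither follows: under randomisation the unadjusted difference is unbiased and the test keeps its level. The loss is precision.
- **No information is lost for planning.** A reader might infer that the t tests deprive the full trial of the residual SD and baseline correlation. They do not, since the questionnaires are collected at baseline and every follow-up and both quantities can be computed whichever test is used. The full trial's main outcomes also include days to return to work, which has no baseline score.
- **Not every secondary outcome is affected.** Satisfaction with return to work and job satisfaction are asked only after return, and participants are not working at entry. No baseline is described for satisfaction with the return-to-work process either. Among the named secondary outcomes the point covers mood, quality of life and illness perceptions.
- **Stratification adjustment is not a sure gain.** It fits the design, but it costs 4 more df and lowers power if the covariates predict little. The full-trial ANCOVA as described covers baseline values only.
- **The correlation is unknown.** This is true, which is why the range starts at zero. The possible loss is under one point of power and the possible gain is large.
- **Little depends on these tests.** The main analysis is qualitative and the study is not for hypothesis testing. That limits the weight of the point but does not make the rationale right.

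**Conclusion.** The point holds for secondary outcomes with a baseline score. Insufficient power is not a reason to prefer an unadjusted t test. At N = 60 baseline adjustment costs at most about 0.7 points of power, and it gains once the correlation passes about 0.14: about 3, 11 and 27 points at 0.3, 0.5 and 0.7. These figures rest on an assumed effect of 0.5 SD, a two-sided test, 30 analysed per arm and assumed correlations. With 20 per arm the conclusion is the same and break-even is about 0.17. The consequence is avoidable imprecision in exploratory comparisons and a missed rehearsal of the definitive analysis; it does not make the results invalid. The change is worth making because it is almost free.

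**What to change.** 1. For secondary outcomes with a baseline score (HADS mood, illness perceptions, EQ-5D-5L, quality-of-life visual analogue scale, and the Work Ability Index if it is analysed), replace the t test with ANCOVA of the follow-up score on arm and baseline score. Report the adjusted mean difference with a 95% CI, the residual SD and the baseline-to-follow-up correlation. Estimates with intervals also suit a study that is not testing hypotheses.
2. Leave outcomes asked only after return to work outside the baseline adjustment, and say so.
3. Decide in advance whether age group and cancer type enter the model. Including them is consistent with the stratified design, but uses 4 more df and gains power only if joint R exceeds about 0.30.
4. Reword the power sentence to say that 60 participants are too few for confirmatory inference by any method, without singling out ANCOVA.

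The cost is wording and one residual df per model (57 instead of 58). No new data or participants are needed.
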